### Dissemination

Upon completion of data analysis, a one-page summary of the research results will be made available on the Black Dog Institute website and will be emailed to all parents of participants. We will encourage parents to share the findings with their child. The research team will prepare the trial outcomes for publication in relevant peer-reviewed journals and present outcomes at scientific conferences. To comply with the National Health and Medical Research Council open access policy, the researchers will make efforts to publish all papers resulting from this research in open access journals. In all reports, participants will not be individually identifiable and numerical data will be presented in aggregate form. Any qualitative data reported will be represented with non-identifiable codes.

## Discussion

This protocol outlines a clinical trial that aims to examine the effect of a CBT-I smartphone app (Sleep Ninja) on insomnia symptoms and other mental health symptoms in children aged 10- to 12 years experiencing frequent sleep disturbance. To the best of our knowledge, this will be the first study to evaluate app-delivered CBT-I in children with sleep difficulties. Sleep Ninja was originally developed collaboratively with young people, to address a lack of digital, self-guided CBT-I programmes to improve adolescent sleep and mental health symptoms [22]. Sleep Ninja has been shown to improve sleep and depression in adolescents experiencing insomnia symptoms [17]. With high rates of insufficient and disturbed sleep occurring in children and rising rates of childhood depression [54], alongside limited access to appropriate care [55], access to evidence-based care is needed. If found to be effective, Sleep Ninja has the potential to provide an accessible, free, and scalable treatment to improve insomnia and possibly other mental health symptoms in children. The outcomes of this trial will contribute to our understanding of utilising digital technologies to support children experiencing sleep difficulties and inform innovations in the field.

### Strengths

This is the first randomised controlled trial to evaluate app delivered CBT-I in children under 12 years with frequent sleep disturbance. The intervention under evaluation provides a brief, self-guided and time efficient treatment, which is a treatment option for sleep not currently available for 10 to 12 year olds. The trial design includes an active control condition that allows evaluation of the effect of Sleep Ninja beyond non-therapeutic effects, such as knowledge gained from generic sleep information widely available online and parental engagement. The sample size (N = 214) will ensure adequate power to detect intervention effects on insomnia. Finally, this study improves on previous studies by assessing diagnostic criteria for MDD. Although base rates of depression in this age group are low [56, 57], using diagnostic criteria as assessed by the KSADS-COMP goes beyond symptom measures and ensures the sample in this study do not have a history of depression, thereby allowing exploration of the notion that treating sleep reduces risk of subsequent depression.

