To overcome the lack of accessible CBT-I for older children, our research team has adapted the Sleep Ninja smartphone application [20] for use among children aged 10 to 12 years old. The Black Dog Institute originally developed Sleep Ninja, a free, fully automated CBT-I smartphone application designed in consultation with adolescents and their parents [21], for adolescents aged 12 to 16 years. Sleep Ninja contains six brief lessons or ‘training sessions’ (each up to ten minutes in duration), that deliver core components of CBT-I, including psychoeducation, stimulus control, sleep hygiene, and sleep-focused cognitive therapy. It uses gaming elements to enhance user engagement, which are based on a Ninja analogy with users ‘levelling up’ on completion of a training session until they master sleep skills and become a black belt in sleep.

Previous research shows Sleep Ninja improves insomnia and reduces depression symptoms in adolescents relative to an active control, with superior effects for younger teenagers [17, 22]. Given its gamified features and readability level (i.e., for readers at the Year 5 to 6 level, aged 10 to 12 year old) of the original Sleep Ninja app, and children’s increased capacity to use interactive smartphone applications [23], Sleep Ninja required only minor modifications for adaption for 10 to 12 year olds. The key modifications included involving parents in the intervention by developing a website containing resources for parents, guardians and carers (henceforth referred to as parents) to support their child’s autonomous use of Sleep Ninja, and ensuring the suggested bedtimes were based on age-appropriate sleep duration recommendations [24]. A clinical trial is now needed to determine the effectiveness of Sleep Ninja for improving insomnia symptoms and other mental health symptoms in primary school children aged 10 to 12 years.

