### Intervention condition

Participants allocated to the intervention condition receive access to the child-adapted version of Sleep Ninja for 6 weeks. Sleep Ninja is an automated smartphone application co-designed with 12- to 16-year-olds and parents to deliver CBT-I. It is free and publicly available in Australia on devices using iOS and Android operating systems. The program includes six sequential modules (referred to as ‘training sessions’), a sleep tracking function, sleep scheduling based on required wake time and age-dependent sleep duration recommendations, personalised wind-down routines and reminders, a series of sleep tips, and general information about sleep. Each training session covers a core CBT-I strategy including: (a) sleep scheduling; (b) stimulus control strategies; (c) sleep hygiene for evenings and daytime; (d) cognitive therapy including how to deal with thoughts that can prevent sleep onset (e.g., repetitive worrying) (e) identification and planning for high-risk situations and diversions from sleep routine; and f) relapse prevention. Sessions are delivered through an automated chat-bot where the Ninja acts as a sleep coach. Sleep Ninja is designed to be used during the day and not at bedtime to prevent device use and blue light interfering with sleep. The child version of Sleep Ninja also includes a website for parents, designed in collaboration with parents. The website contains guidance to assist parents in supporting their child to use Sleep Ninja autonomously and additional resources including information on Sleep Ninja, case examples, frequently asked questions, and contact information for the Child Sleep team at the Black Dog Institute. Parents of participants allocated to receive the intervention will be provided with the URL for the website alongside instructions on how to download Sleep Ninja. Child participants allocated to the intervention condition will be instructed to complete the Sleep Ninja app content by undertaking one ‘training session’ and tracking their sleep for three nights per week (approximately 10 min in duration) for six weeks. One email and one Short Message Service (SMS) reminder will be sent to the parents of participants who fail to download the Sleep Ninja app within 7 days of randomisation. Participants who do not download the app will remain in the trial and be included in the intention-to-treat analyses.

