### Control condition

Participants allocated to the active control condition will receive six digital psychoeducation flyers, delivered weekly, that are optimised for viewing on mobile devices. Psychoeducation is a recognized and well-received intervention for sleep problems and has shown modest positive effects on outcomes without incorporating active cognitive-behavioural therapy (CBT) components [27–29]. Our active control has also been matched to the intervention condition in terms of visual appeal, weekly content dosage, and engagement duration. This provides control participants with helpful but non-therapeutic information related to sleep, thereby minimizing the likelihood of dropout in the control condition [30]. The psychoeducation consists of six topics (taking approximately 10 min to read): (1) Why do we sleep? (2) Fun facts about sleep, (3) Tips to help you sleep-Part 1, (4) Tips to help you sleep-Part 2, (5) Stress and sleep, (6) Where to get more help. The content was created specifically for this trial and to be appropriate for 10 to 12 year olds. The content has a readability score at the Year 5 to 6 level (i.e., for readers aged 10 to 12). All participants in the control condition will be provided with access to Sleep Ninja once their participation in the trial has concluded (i.e., 9-months post-baseline).

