### Sample size

The total sample size required for detecting change in the primary outcome at the primary endpoint was calculated to be 214. This was based on using α = 0.05, power = 0.8 to detect a medium between-group effect size (d = 0.41) [17, 22] on child-reported insomnia outcomes. This estimate accounts for an attrition rate of 40% between baseline and the primary endpoint. The effect size parameter used in the power calculation accounts for potential effects of the active control condition, as seen in the adolescent study [17], but is more conservative than the between-group effect size reported in that study (d = 0.41) due to the differences in the delivery format (parent-supported vs. self-directed).

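### The active control does not balance the parent support website, so the trial cannot show an effect of Sleep Ninja beyond parental engagement

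*Protocol article*

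**What the plan says.** In the Discussion, under Strengths, the protocol article credits the active control with allowing Sleep Ninja to be evaluated "beyond non-therapeutic effects, such as knowledge gained from generic sleep information widely available online and parental engagement".

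Other sections describe parent involvement as part of the intervention:

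- **Introduction:** "The key modifications included involving parents in the intervention by developing a website containing resources for parents, guardians and carers".
- **Intervention condition:** "The child version of Sleep Ninja also includes a website for parents, designed in collaboration with parents". On its purpose: "The website contains guidance to assist parents in supporting their child to use Sleep Ninja autonomously". It also holds case examples, frequently asked questions and contact details for the study team. On who receives it: "Parents of participants allocated to receive the intervention will be provided with the URL for the website".
- **Sample size:** the effect size is discussed against the adolescent study "due to the differences in the delivery format (parent-supported vs. self-directed").

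For the comparator, Control condition says: "Participants allocated to the active control condition will receive six digital psychoeducation flyers, delivered weekly". The control is described as "matched to the intervention condition in terms of visual appeal, weekly content dosage, and engagement duration". No parent material is described for this arm.

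Under Intervention adherence and attrition, the parent-report adherence measure, which contains the parent-involvement items, is given in the intervention group only. The note to Table 1 says the same. For controls, the section records clicks on the flyer links.

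**The concern.** A control condition removes an influence from a treatment contrast only if both arms receive that influence to a similar degree. The Strengths section names parental engagement as something the control removes, yet the article elsewhere describes a tool for involving parents that is part of one arm only.

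What is at stake is the interpretation of a positive result. If Sleep Ninja does better than the flyers, the gain could come from the CBT-I content, from parents who were coached to support the child, or from both. A reader who relies on the Strengths section would conclude that the second explanation had been ruled out. The data planned for collection would not let anyone check, because involvement is not recorded for controls.

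**Working it through.** The point depends on no figure in the document, so no calculation applies. The check sets the descriptions of the two arms side by side.

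| Parent-related feature | Sleep Ninja arm | Flyer arm | Where stated |
|---|---|---|---|
| Screening, consent and registration by the parent | Yes | Yes | Procedure and participant timeline |
| Allocation email to the parent | Yes | Yes | Procedure and participant timeline |
| Parent-report assessments, with reminders | Yes | Yes | Table 1; Procedure and participant timeline |
| Website guiding parents in supporting the child | Yes | None described | Introduction; Intervention condition |
| Email and SMS to the parent if the app is not downloaded within 7 days | Yes | None described | Intervention condition |
| Parent-involvement items at 6 weeks | Yes | No | Intervention adherence and attrition; Table 1 note |

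**Step 1: what is balanced.** The first three rows are the same in both arms. Engagement that arises simply from taking part as a parent is therefore shared, and the control does account for it.

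**Step 2: what is not balanced.** The website differs by allocation. The Control condition section sets out both the flyer content and the matched features. Those features are visual appeal, weekly content dosage and engagement duration; parent support is not among them. The section covers this very topic, so the gap cannot be put down to a shortened article.

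**Step 3: what the contrast estimates.** The arms differ in (a) CBT-I app versus flyers and (b) parent website versus none. With two arms, only the sum of (a), (b) and any interaction between them can be estimated. No arm has the app without the website or the flyers with equivalent parent support.

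**Step 4: whether planned data could help.** The adherence measure has 11 items. The first five cover use and behaviour change, the sixth covers sessions completed, and the remaining 11 − 6 = 5 cover parent involvement. None is put to control parents. Website traffic concerns the intervention material, and flyer clicks do not show what the parent did. The arms therefore cannot even be described side by side on parent involvement.

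**The case against.** The strongest reply is that the website belongs to child Sleep Ninja as the protocol defines it, so its effect is part of the treatment effect and not a confounder. That stands: the randomised comparison is a valid estimate for the package. The objectives and hypotheses claim only superiority relative to the active control, and no planned analysis depends on separating out parental engagement.

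A second reply is that the sentence may refer to generic engagement, which both arms share. Table 1 says the flyers go by SMS, and the mobile number collected at registration is the parent's, so control parents may well be prompted weekly too. This is a fair inference, although the article does not state it. It narrows the fault to the added, structured support. It does not rescue the sentence as written, which makes no such distinction.

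A third reply is that the website aims at the child's autonomous use, so it may raise parental engagement little, and that the parent-supported label in the Sample size section compares this trial with the adolescent study and not the two arms. Both observations are correct. The size of any difference in engagement is unknown. The Introduction nevertheless presents the website as the means of involving parents.

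Two stronger readings are tempting, and the document does not support them:

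- A reader might infer that sleep tracking breaks the match on engagement duration. The stated 10 minutes or so can be read as covering the training session and the tracking together, which agrees with the time given for each flyer topic.
- A reader might infer that parent-reported outcomes are the most exposed. Nothing in the document shows this. If parent support improves sleep, child reports would change as well.

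**Conclusion.** The claim in the Strengths section holds for generic parent contact and fails for the parent support that only the intervention arm receives. The trial can show whether child Sleep Ninja, meaning app plus parent website, does better than psychoeducation flyers. It cannot show that the app's CBT-I content does so apart from the added parent support.

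A reader might go further and infer that the primary comparison is biased or that the control is inadequate. The document does not support that: randomisation protects the package contrast, and the primary outcome, its analysis and the hypotheses are untouched.

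The finding is minor. Its size in outcome units cannot be derived, because the article gives no figure for the effect of the website and plans no comparator data on involvement. The conclusion assumes that control parents receive no equivalent material, as the Control condition section indicates.

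**What to change.** 1. In Strengths, delete the reference to parental engagement, or limit it to the parent contact that both arms share through enrolment and assessment.
2. When conclusions are drawn, state the contrast as Sleep Ninja app plus parent website versus psychoeducation flyers.
3. At 6 weeks, ask control parents the existing items on frequency and duration of involvement, reworded for the assigned activity. Report the result by arm as description only. Involvement arises after randomisation, so adjusting for it would not separate the app from the website.

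The cost is a slightly less favourable claim and a few items added to a survey that control parents already complete at that visit. Randomisation, the interventions, the sample size and the primary analysis stay as they are.

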### Limitations

Given Sleep Ninja is publicly available, contamination bias may occur. To minimise the risk of contamination, Sleep Ninja is not named in any of the recruitment or trial information. The use of sleep applications is also being assessed at each assessment to monitor and identify the use of Sleep Ninja by participants in the control condition. Despite these limitations, the results of this trial will offer valuable insights into the potential of a CBT-I smartphone app to address a gap in the current treatment landscape and shed light on the factors that contribute to therapeutic benefits in children aged 10 to 12 years old.

## Data Availability

Data sharing is not applicable to this article as no datasets were generated or analysed during the current study. A detailed study design and analysis plan were preregistered, including access to material, see https://www.anzctr.org.au/Trial/Registration/TrialReview.aspx?id=385818.

## List of Abbreviations

AE: Adverse Event
CBT: Cognitive Behavioural Therapy
CBT-I: Cognitive behavioural therapy for insomnia
ESS: Epworth Sleepiness Scale
DBAS: Dysfunctional Beliefs and Attitudes about Sleep
DSM: Diagnostic and Statistical Manual of Mental Disorders
ICSD: International Classification of Sleep Disorders
KSADS: Kiddie Schedule for Affective Disorders and Schizophrenia
MDD: Major Depressive Disorder
MMRM: Mixed-model repeated measures
NHMRC: National Health and Medical Research Council
PINTS: Persistent and Intrusive Negative Thoughts Scale
PISI: Paediatric Insomnia Severity Index
PISCF: Participant Information Statement and Consent Form
PSQI: Pittsburgh Sleep Quality Index
RCADS-25: Revised Children’s Anxiety and Depression Scale-25
RCT: Randomised Controlled Trial
SMS: Short Message Service
SAAQ: Sleep Anticipatory Anxiety Scale
UNSW: University of New South Wales
